#### Mechanism of action on primary

If the primary analysis indicates a treatment effect, then we will undertake a mediation analysis to explore the mechanisms underlying the intervention using a structural equation modelling approach. Variables to be included as potential mediators include parental sensitivity (as measured by the NIHD Sensitivity Scales), emotion regulation (as measured by the DERS) and life changes (e.g. the start of social care for the family) and relationship status (as measured by the demographic questionnaire and CSRI).

Pre-specified subgroup analysis will be performed for the primary outcome to explore the uniformity of the treatment effect by adding a treatment-by-subgroup interaction term to the primary analysis model (or test for trend where appropriate) for the following:History of mental health difficultiesExperienced childhood maltreatmentGeographical areaAgeEthnicityDeprivation (as measured by personal gross yearly income)Relationship status

#### Supplementary analyses on primary

We will also undertake supplementary analyses to estimate the intervention effect in those that received the intervention sessions as planned. This is undertaken using a counterfactual approach where we will initially define a ‘complier’ (Y/N) as an individual who attends at least 60% (i.e. 6 of the 10) intervention sessions. We will also examine alternative definitions of a ‘completer’ estimating the effect of attending an increasing number of sessions [1–10].

#### Secondary analyses

Analysis of the secondary efficacy outcomes will be undertaken following the same framework as the primary outcome model with a time-by-intervention interaction using appropriate generalised linear models. For each continuous outcomes including the DERS, PBQ, ASQ-3, ASQ-SE and the NICHD Sensitivity Scales, a mixed effects linear regression model will be fitted as described above for the primary outcome. Trajectories of the predicted estimates with accompanying 95% confidence intervals from the mixed effects models over time will be displayed graphically.

Any secondary binary outcomes will be analysed using a generalised linear model fitted with a binomial distribution and logit link function and treatment effects are reported as odds ratios with 95% confidence intervals. Any secondary categorical outcomes will be analysed using a generalised linear model fitted with a binomial distribution and ologit link function for ordered categorical responses and the mlogit link function for unordered categorical responses and treatment effects reported as odds ratios (ologit model) or relative risk ratios (mlogit model) with 95% confidence intervals.

For the analysis of any time-to-event outcomes, treatment effects will be modelled using a proportional hazards time-to-event model. Kaplan–Meier estimates will also be plotted with confidence intervals for each treatment arm with extended at-risk tables [41].

##### Adverse events

Kaplan–Meier plots are used to examine rates of withdrawals by arm due to any AE. The number of participants requiring social care involvement for the family will be tabulated by arm and Kaplan–Meier plots will be used to examine the time to social care involvement by arm. All AEs are tabulated by arm and severity for the number of participants with at least one adverse event and the number of adverse events. We also calculate odds ratios and incident rate ratios and their 95% CIs for binary and count AE outcomes at SOC level using logistic regression and Zero-Inflated Poisson model or negative Binomial model, following the same framework as the primary analysis model using appropriate generalised linear models with adjustments. The results from these models are then presented graphically along with the raw counts using visual approaches such as the dot plot [42].

A detailed statistical analysis plan will be written prior to data lock and will detail all analysis models and model checks to be performed.

#### Qualitative data analysis

Survey data response rates and descriptives on the demographics of respondents will be summarised in order to describe the sample of respondents. These data and responses to closed questions will be subject to basic descriptive statistics including frequency counts and cross-tabulation. Responses to open-ended survey questions will be analysed using content analysis which involves generating descriptive codes summarising text responses and counting the frequency of those codes within the dataset.

The qualitative data collected during focus groups and interviews regarding parent and staff experiences will be transcribed verbatim by a confidentiality-bound professional transcription service. The data will be managed using NVivo and analysed using the Braun and Clarke thematic analysis approach [43]. Initially, a selection of the transcripts will be independently coded line-by-line by a qualitative sub-team to generate initial codes and search for candidate themes. These will then be reviewed and refined in a face-to-face meeting before undertaking further coding of subsequent transcripts. To promote rigour, peer debriefing will be used, with the researchers scrutinising each other’s interpretations and searching for disconfirming evidence. The emerging themes will be discussed with the EbE panel to ensure credibility and relevance for service users. We will explore alternative interpretations by revisiting transcripts, and refining the analysis supported by a series of remote and face-to-face discussions, until a satisfactory analysis is reached with agreement of final themes. Anonymised quotations will be used to illustrate the themes and a detailed audit trail will be recorded, summarising the development of themes.

#### Economic analysis

We will perform a within-trial economic evaluation comparing the costs and outcomes of COS-P versus TAU. We will assess the costs of implementing and delivering the intervention (e.g. cost of each session, including video projection, practitioner psychologist time) and the cost of TAU. We identify and measure health care resource use (e.g. GP consultations, psychological consultation, medications) through the CSRI [44] and using standard unit costs. The analysis will be performed by adopting the perspective of the UK NHS and Personal Social Services. Outcomes are measured using the EQ-5D-5L questionnaire [45] (but we will also explore translating the CORE-OM [33], and CORE-6D [46] into utility) to generate QALYs for the 12-month follow-up. The economic evaluation estimates the incremental cost per QALY associated with COS-P. Net monetary benefit of the intervention and TAU is assessed using the NICE lower and upper threshold [47]. If there is a significant outcome effect, a decision analytic model will be used to extrapolate the results over the longer term. Sensitivity analysis will be performed to control for uncertainty in the parameters and data.

### Interim analyses {21b}

An internal pilot will be embedded in the trial to assess recruitment rate by site, adherence to the intervention, fidelity to intervention, time to starting the intervention in the intervention arm, number and type of ‘treatment as usual’ received in control and intervention arm and overall trial retention. This information will be reviewed 12 months after recruitment has started. The review of adherence to the intervention and fidelity to intervention will be undertaken by the DMEC and the review of recruitment and retention will be undertaken by the TSC, both consisting of largely independent experts across the fields of mental health, parenting research, health economics, trial statistics and public involvement. We will use a traffic light system and the stop/go criterial can be found in Additional File 2.

### Methods for additional analyses (e.g. subgroup analyses) {20b}

There will be no additional analyses.

### Methods in analysis to handle protocol non-adherence and any statistical methods to handle missing data {20c}

As we target the treatment policy estimand, we will include all participants in the analysis including those that did not adhere to the protocol. A supplementary analysis will be performed using a counterfactual approach to estimate the treatment effect in those that adhered to the treatment protocol. Participants who have missing data points will be included in the analysis under a Missing at Random assumption implicit when using the longitudinal model. If there are more than 5% of participants who withdraw completely from the study or do not complete at least one post-baseline measurement, then we will undertake Multiple Imputations, again making a Missing at Random assumption. We will conduct an additional (sensitivity) analysis using controlled multiple imputation to examine the impact in case of Missing Not At Random (MNAR).

### Plans to give access to the full protocol, participant-level data and statistical code {31c}

The full protocol is made available on the funder’s website. The study team will retain the exclusive use of data until publication of all planned primary and secondary analyses have been completed. Following this, the anonymised quantitative dataset and extracts of the statistical code will be available from the corresponding author on reasonable request.

## Oversight and monitoring

### Composition of the coordinating centre and trial steering committee {5d}

The research team involved in the day-to-day delivery of the trial meets on a weekly basis, while the wider study team meets monthly, to discuss any current issues and updates. The Trial Management Group, including all co-applicants, meet every quarter. Additionally, the trial is supported by a Patient and Public Involvement co-applicant who leads an active Expert by Experience (EbE) panel. The EbE panel consists of around ten panel members and its role is to ensure that the participants’ perspective is kept in mind in every aspect of the COSI Study. The panel meet quarterly to provide feedback on participant facing documents as well as provide useful insights in aiding the smooth operation for the research team and facilitators. Individually, the panel members’ involvement can vary from giving feedback on certain documents/scenarios to database testing that ensures the systems we have in place are user friendly and that the research assistants are equipped to smoothly run study visits. Panel members are also invited to the COSI monthly meetings, where they can share live feedback with the wider research team. The panel also has two subgroups in which they focus on specific aspects on the study. There is the EDI subgroup, who look to ensure that the study is being as inclusive as possible when recruiting parents who are ethnically diverse. They meet on a semi-regular basis to discuss ways in which we can make this study more accessible to them, and things we should take into consideration when communicating with marginalised communities. The other subgroup supports the qualitative aspect of the study. This subgroup meets at four points during the study, to code and share findings from participants during interviews and from facilitators in focus groups.

The Trial Steering Committee (TSC) has been convened to oversee the progress and conduct of the trial, including a selection of the internal pilot criteria. Membership of the TSC includes an independent chair, independent statistician, independent PPI member, independent experts including experts by experience, and representatives of the study team. The TSC met at the beginning of the trial and will meet annually at a minimum for the trial’s duration.

### Composition of the data monitoring committee, its role and reporting structure {21a}

The Data Monitoring and Ethics Committee (DMEC) is fully independent and responsible for overseeing the safety of the trial and a selection of the internal pilot criteria. The DMEC met at the start of the trial and will meet annually at a minimum with meetings taking place prior to the TSC in order to facilitate reporting from the DMEC to the TSC.

### Adverse event reporting and harms {22}

At each follow-up data collection time point, participants are invited to complete a short survey regarding solicited adverse events (both physical and social) experienced during the trial. Adverse events which are not considered to be related to the trial intervention or procedures and are not one of the solicited adverse events detailed in this questionnaire will not be recorded in this way. However, unsolicited adverse events may be reported directly by participants during data collection visits or by the participant’s PMHS. All related adverse and serious events will be reported to the Chief Investigators, TSC and DMEC. In the event of a serious adverse event (SAE) occurring during the subject’s participation in the study, the SAE must be reported to the CI and the Sponsor.

All related and unexpected SAEs will be notified to the Research Ethics Committee (REC) and the Sponsor within 15 days of the Chief Investigator becoming aware of the event. Follow-up of participants who have experienced a related or unexpected SAE will continue until recovery is complete or the condition has stabilised.

Annual safety reporting will be included in the Annual Progress reports submitted to the Sponsor and the Research Ethics Committee, on the anniversary of Ethics approval each year. The Annual Progress Report will detail all SAEs recorded.

If any urgent safety measures are taken, the Chief Investigator/Sponsor shall immediately, and in any event no later than 3 days from the date the measures are taken, give written notice to the relevant REC of the measures taken and the circumstances giving rise to those measures.

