### Criteria for discontinuing or modifying allocated interventions {11b}

Discontinuation of the allocated intervention is possible after a participant withdraws from the intervention and/or trial or based on clinical judgement by the intervention facilitator, e.g. when a participant’s mental health deteriorates and is not advised by their clinician to continue.

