### Provisions for post-trial care {30}

No provisions for post-trial care are in place. Additionally, there is no anticipated harm and compensation relating to harm for trial participation.

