### Outcomes {12}

#### Outcome measures—quantitative data collection

The primary outcome measure is the Clinical Outcomes in Routine Evaluation – Outcome Measure (CORE-OM; [33]), included in all trial assessments. The CORE-OM is a 34-item measure of psychological distress and is one of the most widely used outcome measures in secondary care mental health services.

Secondary outcome measures exploring parent-infant bonding, experienced childhood maltreatment, emotion regulation, parenting quality, health-related quality of life, health service use, child development and attachment style, adverse events, and COS-P cost-effectiveness will also be completed throughout the trial. Details on these measures are provided in Additional File 4.

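### Mental-health deterioration is not described as a solicited adverse event, and no by-arm analysis of CORE-OM worsening is planned, so this harm may be compared unequally between arms

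*Protocol article*

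**What the plan says.** The section on criteria for discontinuing the allocated intervention {11b} lets the facilitator stop COS-P on clinical judgement. Its example is a participant whose "mental health deteriorates and is not advised by their clinician to continue".

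The section on adverse event reporting and harms {22} sets out how harms are collected:
- All participants are invited at each follow-up to complete a survey of "solicited adverse events (both physical and social) experienced during the trial".
- Events not considered related to the trial intervention or procedures that also "are not one of the solicited adverse events detailed in this questionnaire will not be recorded in this way" are left out of that route.
- Otherwise, "unsolicited adverse events may be reported directly by participants during data collection visits" or by the participant's service.
- For a serious event, "the SAE must be reported to the CI and the Sponsor".

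The adverse events part of the statistical methods tabulates all adverse events by arm and severity. It adds odds ratios and incidence rate ratios at system organ class level and Kaplan–Meier plots of withdrawal due to any adverse event. One specific event is singled out: "The number of participants requiring social care involvement for the family will be tabulated by arm".

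The CORE-OM, a measure of psychological distress and the primary outcome, is "included in all trial assessments". Table 2 places it at baseline, 3, 7 and 12 months. The primary analysis section uses it for a mean difference between arms and for posterior probabilities of superiority and of exceeding the 5-point MCID.

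**The concern.** The trial recruits parents with severe and complex mental-health difficulties, and the protocol foresees that some may get worse while in the group. As described, that kind of event falls outside the two categories of the solicited survey. Non-serious deterioration then depends on a relatedness judgement or on someone volunteering it.

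Neither route works alike in the two arms. A TAU participant cannot have an event related to COS-P, participants know their allocation, and COS-P participants see a facilitator weekly. Deterioration could be over-recorded in COS-P because staff are there to notice it, or under-recorded in both arms because it is put down to the underlying illness. The direction cannot be known in advance. The odds ratios and rate ratios by arm would carry that imbalance.

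The primary analysis does not fill the gap as planned, because a favourable mean can coexist with worsening in a minority. At stake is whether the trial can report on this harm on the same footing in both arms.

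**Working it through.** **Sections side by side.** The protocol gives no figure for this harm to reproduce, so the first check is one of reading.

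| Route | Both arms alike? | Non-serious mental-health deterioration |
|---|---|---|
| Solicited survey | Yes | Not in the stated scope (physical and social) |
| Events judged related | No; TAU has no COS-P to relate to | Only if judged related |
| Unsolicited reports | Not assured; optional | Only if someone reports it |
| Serious adverse events | Rule applies to all | Not covered unless serious |
| COS-P stopped by facilitator | No; COS-P only | Counted in one arm at most |
| CORE-OM | Yes, fixed schedule | Measured, but no analysis of worsening stated |

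Only the CORE-OM row is both symmetric and certain to contain the information.

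**What a mean can hide (illustration; the harmed fraction is assumed).** Suppose a fraction f of the 246 COS-P participants worsen by 0.5 per item, the protocol's SD, because of the group. The arm mean moves by f × 0.5, to be compared with the target of 5/34 = 0.147.
- f = 5%: 0.025, which is 17% of the target.
- f = 10% (about 25 participants): 0.05, which is 34%.
- f = 20%: 0.10, which is 68%.

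**How much worsening to expect by chance.** The sample size section gives SD 0.5 and within-subject correlation 0.35. I apply that correlation to baseline and follow-up and assume normality and no mean change.
- SD of change = 0.5 × √(2 × (1 − 0.35)) = 0.5 × √1.3 = 0.570.
- Rise of 0.5 or more: z = 0.5/0.570 = 0.877, upper tail about 19%.
- Rise of 0.147 or more: z = 0.147/0.570 = 0.258, upper tail about 40%.

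These are per visit. If parents improve on average, as is likely after selection on high scores, the shares will be lower.

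**Precision of a between-arm comparison.** Using a share of 19% in each arm and ignoring clustering:
- 246 v 123: SE = √(0.19 × 0.81 × (1/246 + 1/123)) = 0.043, so the 95% interval is about ±8.5 percentage points.
- 208 v 104: SE = 0.047, about ±9.2 points.

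In the 10% illustration, the harmed participants' chance of rising by 0.5 or more goes from 19% to 50%. The arm's share then rises by 0.10 × (0.50 − 0.19) = 0.031, about 3 points. The table would therefore describe and bound the harm; it would not reliably detect a small harmed minority.

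**The case against.** The strongest objection is that mental health is the primary outcome. CORE-OM is collected on an identical schedule in both arms, and the CSRI records service use in both arms at every assessment. A reader might infer that deterioration goes uncounted in either arm. The documents do not support that: the data exist, serious events must be reported, and all recorded adverse events are tabulated by arm. What the article lacks is an analysis of worsening as a harm.

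Second, a reader might infer that the survey covers nothing but physical and social events. That rests on a parenthesis. Details of the measures are in Additional File 4, which is not shown, so mental-health items cannot be ruled out.

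Third, deterioration is given as an example for stopping COS-P, not as the sole reason, and nothing says that COS-P causes it. Nor does the statement that "there is no anticipated harm and compensation relating to harm for trial participation" contradict this. It sits under post-trial care, and expecting no harm from taking part is compatible with foreseeing that an ill parent may worsen.

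Fourth, analysis detail is deferred to a statistical analysis plan, where a table of worsening could appear. That is fair for the table. It does not dispose of the recording rules, which are stated in the protocol; an analysis plan cannot recover events that were never recorded.

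Finally, the harmed fraction in the illustration is assumed, and any threshold on individual change catches ordinary fluctuation. Both points stand, and they limit how the table may be read.

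**Conclusion.** The point holds in a limited form. As described, the both-arm survey does not name mental-health events. Non-serious deterioration depends on routes that cannot work alike in the two arms, and the article nevertheless compares adverse events by arm. CORE-OM offers a symmetric measure, but is used only for means and probabilities of benefit.

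The size of any imbalance cannot be computed from the documents. The calculable part is the background: about 19% (threshold 0.5) or 40% (threshold 0.147) rising by chance at a visit, under SD 0.5, correlation 0.35, normality and no mean change. A count in one arm alone therefore means nothing; only the between-arm difference does, and for the 0.5 threshold it would be known to roughly ±9 percentage points. This is an inexpensive improvement to harm reporting. It does not threaten the validity of the primary analysis.

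**What to change.** Before data lock:
1. Prespecify a by-arm table, with a between-arm difference and 95% confidence interval, of participants whose CORE-OM mean item score rises above baseline by a stated threshold at 3, 7 and 12 months. The protocol's own figures offer 0.147 and 0.5. State the choice in advance and interpret only the difference between arms.
2. Report COS-P stops for deterioration as a separate COS-P-only count, outside the between-arm comparison.
3. Do not base the by-arm comparison of unsolicited adverse events on judged relatedness.
4. If the survey already contains mental-health items, correct its description in the section on adverse event reporting and harms {22}.

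The cost is one extra table from data already collected, with a threshold that also counts some ordinary fluctuation. Adding survey items now is less attractive: recruitment is under way, an amendment needs approval by the funder, trials unit, Expert by Experience panel and ethics committee, and the new items would miss participants already followed up.

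### Non-serious unsolicited adverse events are not ascertained alike in the two arms, yet the planned between-arm odds and rate ratios are not restricted to events that are

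*Protocol article*

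**What the plan says.** Adverse event reporting and harms {22} describes these streams:

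- **Solicited events.** At each follow-up, "participants are invited to complete a short survey regarding solicited adverse events (both physical and social) experienced during the trial". This applies to both arms and carries no relatedness condition.
- **Other events, by that route.** One class of events is set apart: "Adverse events which are not considered to be related to the trial intervention or procedures and are not one of the solicited adverse events". Relatedness to the intervention or to trial procedures is thus a criterion for recording a non-solicited event. What the sentence goes on to say about this class concerns the survey route: "detailed in this questionnaire will not be recorded in this way".
- **Other events, by direct report.** The next sentence adds that "unsolicited adverse events may be reported directly by participants during data collection visits" or by their perinatal service. It sets no relatedness condition, and it does not say whether such reports are entered as data.
- **Onward reporting and SAEs.** "All related adverse and serious events will be reported to the Chief Investigators, TSC and DMEC". For any SAE during participation, "the SAE must be reported to the CI and the Sponsor", again with no relatedness condition.

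The Adverse events paragraph under Secondary analyses tabulates all adverse events by arm and severity. It continues: "We also calculate odds ratios and incident rate ratios and their 95% CIs for binary and count AE outcomes at SOC level", with the results shown in dot plots. Nothing limits these comparisons to a particular stream.

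**The concern.** A ratio between arms describes safety only if an event has the same chance of reaching the dataset in either arm. That holds for the solicited survey. It is doubtful for non-serious unsolicited events, because relatedness to COS-P is tied to exposure, and spontaneous reporting depends on who is in contact with whom and on what participants know about their allocation. Both features push towards more recorded events in the COS-P arm.

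The analysis is by system organ class (SOC), so a class with few solicited items would rest mainly on the unevenly collected stream. An apparent excess there could reflect the recording rule rather than harm, and it would be published with a confidence interval that does not reflect this.

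**Working it through.** The article gives no adverse event rate, so there is no stated figure to reproduce. The check has two parts.

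**1. Two readings of the recording rule**

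*Reading A: the relatedness criterion decides what is recorded.* The section on concomitant care {11d} rules out offering COS-P to controls. A control event can therefore qualify through trial procedures, but hardly through the intervention. A COS-P event can qualify through either.

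*Reading B: direct reports enter whatever their relatedness.* The reporters are participants, who are not blinded (Procedure for unblinding {17b}), and the perinatal services. Service staff deliver COS-P in ten weekly 90-minute sessions (Intervention description {11a}). They are encouraged to make pre-group calls and to contact anyone who misses a session, and catch-up sessions are offered (Strategies to improve adherence {11c}). The article describes no matching trial contacts for controls. Reporting is optional and unprompted.

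Neither reading gives equal ascertainment of non-serious unsolicited events.

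**2. What unequal capture would do to the ratios**

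All inputs here are assumptions, with the same true risks in both arms:

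- s = risk of at least one solicited event: 0.1 to 0.5
- u = risk of at least one unsolicited event, independent of s: 0.1 to 0.3
- f = share of unsolicited events that reach the dataset, which may differ by arm

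Recorded risk in an arm: p = 1 − (1 − s)(1 − u·f). Apparent odds ratio: [p₁/(1 − p₁)] / [p₀/(1 − p₀)], where 1 is COS-P and 0 is TAU.

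Example with s = 0.3, u = 0.2, f = 0.3 in COS-P and 0.1 in TAU:

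- p₁ = 1 − 0.70 × 0.94 = 0.342
- p₀ = 1 − 0.70 × 0.98 = 0.314
- odds ratio = (0.342/0.658) / (0.314/0.686) = 1.14

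| s | u | f 0.1 vs 0 | f 0.3 vs 0 | f 0.3 vs 0.1 | f equal |
|---|---|---|---|---|---|
| 0.1 | 0.1 | 1.10 | 1.31 | 1.19 | 1.00 |
| 0.1 | 0.3 | 1.31 | 1.99 | 1.52 | 1.00 |
| 0.3 | 0.2 | 1.07 | 1.21 | 1.14 | 1.00 |
| 0.5 | 0.1 | 1.02 | 1.06 | 1.04 | 1.00 |
| 0.5 | 0.3 | 1.06 | 1.20 | 1.13 | 1.00 |

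The distortion is small where solicited events dominate (1.02 to 1.20 at s = 0.5) and larger where they are few (1.10 to 1.99 at s = 0.1, with f = 0 in TAU). It vanishes when the captured share is the same in both arms.

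For an SOC made up only of unsolicited events with equal true rates, the incidence rate ratio is simply f₁/f₀. With 0.3 against 0.1 that is 3.

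**The case against.** A reader might infer that unsolicited events are kept only when judged related, that controls can contribute none, and that the plan therefore builds in a bias against COS-P. The article does not support this:

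- The exclusion is limited to the survey route ("detailed in this questionnaire will not be recorded in this way"), and the next sentence opens direct reporting with no relatedness condition.
- Relatedness includes trial procedures, which both arms undergo, so controls are not shut out.
- Nothing says that whoever judges relatedness knows the arm. The assessor is not named, and the researchers who collect quantitative data are blinded.
- No count of excess events can be derived. The rates are not given, and the safety population in the COS-P arm is those attending at least one session, not all 246 randomised.

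It can also be said that both arms are under a perinatal service and share the same follow-up schedule, that solicited events and SAEs escape the criterion, and that a full protocol and an analysis plan may hold the missing rule.

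All of this limits the point, but a core remains. Shared visits do not remove the extra COS-P contacts or the participants' knowledge of their arm. Details left to other documents are not the issue. The article states a recording criterion tied to exposure and an unrestricted comparison, and the two do not fit together. An analysis plan can restrict the comparison, but it cannot recover events that were never recorded.

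**Conclusion.** The point stands as a risk, not as a demonstrated bias. The article leaves it unclear whether unrelated unsolicited events enter the dataset, and on either reading non-serious unsolicited events are not collected alike in the two arms. Unrestricted odds ratios, rate ratios and dot plots could therefore overstate harm in COS-P.

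The size is unknown. The range of 1.02 to 1.99 for an apparent odds ratio with no true difference rests wholly on assumed rates and on a higher captured share in COS-P. With equal capture the ratio is 1.00. The calculation is for any event, whereas the plan models by SOC, where the effect would vary with the share of solicited items. The solicited survey, SAE reporting and the primary analysis are not affected by the relatedness criterion. The change is worth making because it is cheap and removes a source of misleading safety comparisons.

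**What to change.** 1. In the harms section, state the recording rule: whether unsolicited events reported directly by participants or services are entered in the dataset when they are not considered related. Reconcile it with the statement in the analysis section that all adverse events are tabulated.
2. Base the between-arm odds ratios, incidence rate ratios and dot plots on the solicited survey events plus SAEs recorded regardless of relatedness.
3. Tabulate other unsolicited events by arm, descriptively, with a note on how they came to be recorded.

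This is a change of wording to the reporting rule and the safety analysis. It needs no new data and leaves the primary analysis alone. The cost is that non-serious unsolicited events get no formal comparison, so a real difference confined to them would be seen only in the descriptive tables.
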